### 2.4. Measure of the Behavioural Markers of Apathy

As shown in Figure 2, the behavioural markers of apathy will be assessed in both patient-caregiver dyads and healthy control dyads using behavioural metrics extracted from the dyad’s raw behavioural data. The raw behavioural data of a dyad is made of: (1) passive data, collected continuously, from the multi-sensor wearable bracelet in both members of the dyad; (2) active data, collected once a week during the four weeks of monitoring, from a questionnaire filled by one partner of the dyad (for patient-caregiver dyads, this will be the caregiver) using a smartphone application. For the monthly scale assessment, only the passive data throughout the 28 days will be used to extract the behavioural metrics whereas for the daily scale assessment, both the active and passive data throughout the 24 h will be used.

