### 1.1. Assessment Limits and the Potential of Information and Communication Technologies

A first limitation regarding the assessment of apathy is due to its definition, which remains controversial. Robert Marin proposed that apathy corresponds to a ‘lack of motivation not attributable to diminished level of consciousness, cognitive impairment or emotional distress’ [10,11]. However, the concept of ‘lack of motivation’ is a projective psychological interpretation of a given behavioural state and as a syndrome, apathy should be objectively described, regardless of any psychological interpretation. This is the reason why apathy has more recently been defined, from a behavioural perspective, as the reduction of voluntary and purposeful behaviours [12,13]. Goal-directed behaviours (GDB) are observable and thus, more easily quantified. Moreover, apathy is usually assessed with clinical scales based on Marin‘s definition, with questions about internal state, thoughts and past activities suggesting a loss of motivation to perform daily activities (e.g., the Apathy Evaluation Scale [14]). These scales are thus biased by the subjective perspective of patients’ or caregivers’ point of view and they do not allow a precise description of apathetic behaviour in everyday life [15]. Besides, important discrepancies are often observed between patient’s and caregiver’s reports, especially in neurological conditions such as AD and FTD in which anosognosia causes a lack of awareness of symptoms [15].

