#### 2.3.2. Recruitment and Inclusion Criteria

Patient-caregiver dyads will be recruited through neurological consultations by the neurologists of three neurological care units of the Salpêtrière hospital in Paris, France. Healthy control dyads will be selected using advertisements on dedicated websites.

Both patient-caregiver dyads and healthy control dyads should be couples living together at home either in a marital or non-marital status and both partners should own a smartphone. Moreover, individuals with dementia of patient-caregiver dyads should meet the following inclusion criteria:Diagnosis of bvFTD according to Rascovsky’s international criteria [42] for the bvFTD group/diagnosis of AD according to Dubois’s international criteria [44] for the AD group;No evidence of any other cerebral pathology;A Mini-Mental State Evaluation (MMSE) score superior or equal to 10 (to minimise the effect of confounding factors related to very severe cognitive impairment);Aged between 40 and 85;No evidence of any psychiatric condition and a Montgomery-Åsberg Depression Rating Scale (MADRS) score inferior to 20 (to avoid confusion between depression and apathy);No evidence of excessive consumption of psychotropic drugs—for instance benzodiazepines, sleeping pills, etc. (due to their tranquilising effect);No major physical disability disrupting mobility;No heart pacemaker (which would compromise heart rate measuring).

As for caregivers and partners of healthy control dyads, they must similarly comply with the following inclusion criteria:Aged between 40 and 85;No evidence of any psychiatric condition;A MADRS score inferior to 20;No evidence of excessive consumption of psychotropic drugs;No major physical disability disrupting mobility;No heart pacemaker.

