#### 2.4.2. Processing of Active Behavioural Data from Questionnaires

The questionnaire was completed once a week on a smartphone application and refers to five moments of the day: bedtime (3 items), wake time (3 items), breakfast (6 items), lunch (6 items), and dinner (6 items) (see Supplementary Materials, File S1 for further details on the item content of the questionnaire). In patient-caregiver dyads, these questions are completed by the caregiver who reports on the patient’s behaviour. Bed and wake time items will mostly allow to extract behavioural metrics related to the quality of sleep whereas mealtime items are used for the extraction of metrics associated with daytime activity and emotional arousal.

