### 2.7. Data Flow

All the information collected during Visit 1 will be registered using REDCap^®^ (version 10.9.4) secure web application. These data will be stored on the local secure server (of Paris Brain Institute, Paris, France).

During the 28-day follow-up, remote data collection will require two steps (see Figure 4):Collection of two types of data through an application installed (by the investigators) on patients’ and caregivers’ smartphones: data from sensors (passive behavioural data), and data from questionnaires (active behavioural data + caregiver’s perception of the dyad’s psychological state);Transfer of these data to a remote server application hosted by a local secure server (of the Paris Brain Institute).

Data from the sensors of the E4 bracelet will be continuously collected in both partners of the dyad and transferred to their smartphone application in real-time, each bracelet being paired with its carrier’s smartphone. In case of connection loss with the paired bracelet, the application will send a push notification to warn the participant. Data from questionnaires will be collected directly through the application, sending reminder notifications to the caregiver in patient-caregiver dyads (or to one of the partners, randomly selected, in control dyads).

After being encrypted, all the data collected by the application will be temporarily stocked on the smartphone and progressively transferred to the remote server application hosted by the local secure server. All the data collected by the application will be anonymised and identified only through the associated time-stamp and individual PIN code attributed to each participant of the study.

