#### 2.8.2. Analysis Plan for Primary Objective

First, we will extract the metrics from both passive and active behavioural data on a monthly and a daily basis for all dyads. Using these metrics, we will explore a measurement model for the three assumed behavioural markers of apathy on the two time-scales (with monthly scale metrics for the monthly scale model and daily scale metrics for the daily scale model).

We will use Exploratory Factor Analysis (EFA) and Confirmatory Factor Analysis (CFA) in order to identify the system of metrics organised between the three markers, which is the most adapted to measure them. Statistical criteria for the validation of the measurement model tested in CFA (i.e., Root Mean Square Error of Approximation < 0.08, Standardized Root Mean Square Residual < 0.08, Comparative Fit Index > 0.9, Tucker-Lewis Index > 0.9) will guarantee its good adjustment to the data. The internal consistency of the measures of the three behavioural markers will be assessed using Cronbach’s alpha (>0.70). The reliability of the measures (on a daily scale) will also be evaluated through the correlations between the behavioural marker scores obtained on four time-steps (once a week) during the 28-day follow-up (high correlation indicating high reliability).

We will compare the measurement models and mean scores on the three behavioural markers of apathy between groups of patient-caregiver dyads and control dyads (on two time-scales). We will demonstrate that the patient-caregiver dyad’s scores on the three assumed markers of apathy can predict the dyad’s psychological state (as perceived by the spouse caregiver) using linear regression models on the monthly and daily scales. In a perspective of precision medicine, we will also investigate the disentangling of different profiles of apathy, using clustering analyses from the calculated behavioural markers of apathy.

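### On the daily scale, a patient-control difference in marker scores cannot be attributed to behaviour alone, because the scores include ratings by spouses who know the diagnosis

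*Protocol article*

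**What the plan says.** All places are in the protocol article.

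- **What each score contains.** Section 2.4 separates the two time-scales. On the longer one, "For the monthly scale assessment, only the passive data throughout the 28 days will be used to extract the behavioural metrics". On the shorter one, "for the daily scale assessment, both the active and passive data throughout the 24 h will be used".
- **Who rates.** Section 2.4.2 says that in patient-caregiver dyads "these questions are completed by the caregiver who reports on the patient’s behaviour". In control couples, section 2.7 sends the questionnaire reminders to the rater, described as "or to one of the partners, randomly selected, in control dyads".
- **What is rated.** Section 2.4.3 assigns questionnaire metrics to every marker: how much the partner takes part in mealtime tasks (daytime activity), trouble waking and tiredness (sleep), and the rater's impression of emotional response at meals (arousal). Some sleep metrics rest on reported clock times.
- **How groups are formed.** Section 2.3.2: "Patient-caregiver dyads will be recruited through neurological consultations by the neurologists of three neurological care units". Controls come through advertisements.
- **What is tested.** Section 2.1.1 requires valid markers to separate patient couples from healthy couples. Section 2.8.2 compares measurement models and "mean scores on the three behavioural markers of apathy between groups of patient-caregiver dyads and control dyads (on two time-scales").
- **The article's own view of informant reports.** Section 1.1, on existing clinical scales completed by patients or caregivers: "These scales are thus biased by the subjective perspective".

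**The concern.** The rater's knowledge coincides exactly with study group. A caregiver judging a spouse with diagnosed dementia may expect less engagement or feeling, or may compare with how the spouse used to be. A partner judging a healthy spouse has no such frame. Choosing the control rater at random balances the two partners within control couples, but does nothing about the contrast between groups.

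At stake is the meaning of a positive daily result. Section 2.1.1 sets out to validate two models, one per time-scale, so the daily model needs its own evidence. If its scores differ between groups, the planned analysis cannot say whether sensed behaviour, spouse expectation or both produced the difference. The next step described in section 3.3 is a system that runs on sensor data alone, and a daily difference carried by the ratings would not support it.

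**Working it through.** The plan gives no figure for this comparison, so there is none to reproduce. Its 94.2% power in section 2.8.1 concerns overall model fit, not group differences. It does reproduce (591 df, N = 60, assumed RMSEA 0.05 v 0.08, 5% level).

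**Is the path from rater to test complete?** Ratings enter the daily score (2.4), reach all three markers (2.4.3), come from raters whose knowledge equals group (2.3.2, 2.4.2, 2.7), and the score is compared between groups as a validity test (2.1.1, 2.8.2). The article describes no independent rater and no passive-only daily comparison. The fallback in section 3.2 removes the caregiver's sensor data, not the caregiver's ratings.

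**How large could it be?**

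Inputs from the article: 40 patient dyads (20 + 20) and 20 control dyads (2.2); 36 metrics for 3 markers (2.8.1), so 36/3 = 12 per marker on average.

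Assumptions, none of them in the documents: equal weights; one score per dyad; no true group difference; common inter-metric correlation ρ of 0.3 or 0.5; a = 2 to 6 of the 12 metrics rated; expectation shifts each rated metric by δ = 0.3 to 1.0 SD, in the same direction.

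Formulas:

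- SD of the mean of 12 standardised metrics: √[(1 + 11ρ)/12], which is √(4.3/12) = 0.599 at ρ = 0.3 and √(6.5/12) = 0.736 at ρ = 0.5.
- Spurious standardised difference: d = (aδ/12)/SD.
- Rejection probability: two-sided 5% t test, 58 df, noncentrality d × √(40 × 20/60) = 3.651d.

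Example: a = 3, δ = 0.5, ρ = 0.3 gives a shift of 0.125, d = 0.125/0.599 = 0.21, noncentrality 0.76 and rejection in 12%.

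| Rated metrics of 12 | δ (SD) | ρ = 0.3: d, rejects | ρ = 0.5: d, rejects |
|---|---|---|---|
| 0 (passive only) | – | 0, 5% | 0, 5% |
| 2 | 0.3 | 0.08, 6.0% | 0.07, 5.7% |
| 2 | 0.5 | 0.14, 7.9% | 0.11, 6.9% |
| 3 | 0.5 | 0.21, 12% | 0.17, 9% |
| 3 | 1.0 | 0.42, 32% | 0.34, 23% |
| 6 | 0.5 | 0.42, 32% | 0.34, 23% |
| 6 | 1.0 | 0.84, 85% | 0.68, 68% |

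**All three markers.** The criterion in section 2.1.1 speaks of three markers; the table covers one. By simulation with the same d on each marker and inter-marker correlation from 0 to 0.8, all three reject together in at most about 5% of studies at d = 0.21 and below about 20% at d = 0.42. Only the most extreme row (d = 0.84) gives a high joint rate, of the order of 60% to 75%.

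**The case against.** The strongest reply has five parts.

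1. *Combining sources is deliberate.* Section 2.1.1 hypothesises that active and passive data together measure the markers better, and a spouse cannot be masked to the partner's diagnosis. This stands: the combined score is legitimate and should stay. It does not help to interpret a group difference in that score.

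2. *Other planned analyses would expose the problem.* Section 2.8.2 also compares measurement models between groups, and a shift confined to rated metrics could appear there. Secondary analysis D (2.8.3) asks whether sensor data predict the questionnaire data. Both are relevant. But the article ties no consequence for the mean comparison to the first, and the second does not test the group difference.

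3. *The bias is already acknowledged.* Section 3.2 concedes that caregivers' reports may be biased, but through awareness raised by the monitoring; it makes no link to the group comparison.

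4. *The subjective share is unknown.* Item wording is in a supplement not shown, and some sleep metrics are clock-based. This stands and is why the table spans a wide range.

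5. *Passive-only scores are a different instrument.* This stands too. Passing on passive data would not by itself validate the combined score, so the passive-only result should accompany the combined one and not replace it.

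A reader might also infer that the article promises a measure free of caregiver opinion. It does not: section 3.3 claims independence from the patient's self-report, and the criticism in section 1.1 is aimed at clinical scales about internal states and past activities, not at reports on the day's meals and sleep.

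**Conclusion.** The point holds for the daily scale. Spouse ratings and knowledge of the diagnosis enter the compared scores together, and the stated plan does not separate them from sensed behaviour. A difference in the combined daily score therefore cannot be attributed to behaviour alone. The monthly comparison does not have this problem.

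The size is uncertain. With no true difference, one marker is declared different in about 6% to 85% of studies over the assumed range, against 5% for passive-only scores. The top of that range needs half the metrics rated and a full 1.0 SD shift; with 2 of 12 rated and a 0.5 SD shift the figure is about 7% to 8%.

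A reader might infer that rater expectation alone is likely to carry the daily model through its validity test. The documents do not support that: they give neither the shift nor its direction nor the share of rated metrics, and rejection is less frequent if all three markers must differ. A true behavioural difference may well exist; the difficulty is that the combined comparison cannot show it by itself.

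**What to change.** In section 2.8.2, keep the combined daily score and add that the daily patient-control comparison will also be reported (a) for a score built from the passive metrics only and (b) for the spouse-rated metrics separately, labelled as rated with knowledge of the diagnosis. State that the daily markers will be said to distinguish the groups on behaviour only if the passive-only comparison also shows the difference.

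No new data are needed, since both partners wear the bracelet in all three groups. The cost is an additional scoring step, with its own reliability check because the passive-only score has fewer indicators. The passive-only test also gives up whatever true information the ratings carry. The combined score remains available for the prediction and other analyses.

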#### 2.4.1. Processing of Passive Behavioural Data from Sensors

Using validated algorithms, metrics will be extracted from the data of three sensors in both members of the dyad (for the daily and monthly scales): (1) metrics from the acceleration signal; (2) metrics from the skin conductance signal, and, (3) metrics from the Blood Volume Pulse (BVP) signal.

*Acceleration signal*: We will use a validated signal processing algorithm based on aggregation methods to extract «activity counts» from the raw data of acceleration. Using the validated Cole-Kripke algorithm (an automatic scoring method to distinguish sleep from wakefulness based on wrist actigraphy), we can also detect falling asleep and waking times from the acceleration signal.*Skin conductance signal*: Skin conductance data are traditionally interpreted using validated algorithms that extract two metrics: phasic skin conductance and tonic skin conductance. Phasic changes usually appear as abrupt increases (“peaks”) in the skin conductance. These are generally referred to as Galvanic Skin Responses (GSRs). Tonic skin conductance corresponds to the raw level of conductance of the skin and is usually referred to as Galvanic Skin Level (GSL). Further metrics such as storms (minimum of 5 GSRs/min for at least 10 consecutive minutes) can subsequently be derived from skin conductance data.*BVP signal*: The heart rate is computed by detecting peaks (beats) from the BVP data and computing the lengths of the intervals between adjacent beats. The inter-beat-interval (IBI) timing is used to estimate the instantaneous heart rate (HR), the average HR over multiple beats, and the heart rate variability (HRV) spectrum.

Aside from validated algorithms, we will also use functional principal component analysis (fPCA) to extract metrics from raw sensor data: strings of raw data for a given period can be fit with Fourier-based functions and the equations describing these fits are subjected to fPCA, which allows to reduce the complexity of the data sets through the extraction of only several components (see for instance Zeitzer et al. [29] using acceleration signals).

#### 2.4.2. Processing of Active Behavioural Data from Questionnaires

The questionnaire was completed once a week on a smartphone application and refers to five moments of the day: bedtime (3 items), wake time (3 items), breakfast (6 items), lunch (6 items), and dinner (6 items) (see Supplementary Materials, File S1 for further details on the item content of the questionnaire). In patient-caregiver dyads, these questions are completed by the caregiver who reports on the patient’s behaviour. Bed and wake time items will mostly allow to extract behavioural metrics related to the quality of sleep whereas mealtime items are used for the extraction of metrics associated with daytime activity and emotional arousal.

#### 2.4.3. Metrics for Daytime Activity, Quality of Sleep, and Emotional Arousal

*Daytime activity*: After extracting the activity counts and distinguishing periods of wake and sleep from the acceleration signal, it is possible to calculate more elaborated metrics such as the mean number of activity counts per minute during daytime. We will also detect bouts of activity (sustained periods of elevated counts), bouts of sedentary time (sustained periods of low counts) and compute their mean frequency and duration during daytime. Using active data, we will assess the perceived partner’s investment in several activities at mealtimes: cooking, cleaning, washing the dishes, etc., which will also be useful as complementary daytime activity metrics.

*Quality of sleep*: After extracting the activity counts and distinguishing periods of wake and sleep from acceleration signal, metrics such as total sleep time, wake time after sleep onset, frequency, and duration of activity bouts during night-time will be extracted. We will also integrate metrics extracted from skin conductance and BVP signals during sleep as potential markers of the quality of sleep. The active data enable the calculation of additional metrics such as total time in bed (time between reported bed and wake times), sleep latency (time between reported bedtime and estimated sleep onset), difficulty to wake up and signs of fatigue for one of the dyad partners (patient in patient-caregiver dyads).

*Emotional arousal*: We will use metrics extracted from skin conductance and BVP signals. Metrics derived from the phasic parameter of skin conductance (GSRs) will enable the evaluation of emotional responses to short-term events (e.g., environmental stimulations). Metrics related to the variability of HR (HRV spectrum) are also considered as measures of emotional arousal. Active data will provide complementary metrics such as the perceived partner’s emotional response during interactions at mealtimes.

### 2.6. Procedure

#### 2.6.1. Visit 1 and Visit 2

At visit 1 (see Table 1), the recruited dyads come to the Paris Brain Institute (ICM, Paris, France) at the Centre d’Investigation Clinique Neurosciences (CIC Neurosciences), located at the Salpêtrière hospital in order to: (1) complete the inclusion process; (2) undertake several tests to assess the severity of dementia and of specific clinical symptoms (related to the study); (3) receive all the material for the remote follow-up and be trained to use it. At visit 1, we assess self-reported apathy using two complementary questionnaires: the Apathy Scale (AS) [45] and the Dimensional Apathy Scale (DAS) [35]. The AS is a clinical scale assessing apathy defined as a unidimensional construct linked with general lack of motivation [45] whereas the DAS measures three different underlying dimensions of apathy [35]. Indeed, the DAS consists of three subscales respectively measuring the Emotional, Initiation, and Executive subtypes of apathy inspired by the theoretical model of Levy and Dubois [12,15]. These questionnaires will be useful to investigate the relationships between the behavioural markers of apathy (calculated from passive and active data collected during the remote follow-up—see Section 2.4.1, Section 2.4.2 and Section 2.4.3) and self-reported apathy.

Visit 2 at the Paris Brain Institute (ICM) occurs to return the material and for a feedback session with the couple (perceived benefits, burden of the protocol, potential improvements).

#### 2.6.2. Planning of Remote 28-Day Follow-Up

The remote follow-up of a couple lasts for 28 days during which partners should adopt their usual way of life. The follow-up starts at T0, on the morning of the first Monday after visit 1 and ends at T0 + 28 days, on the morning of the fourth Monday after T0 (see Figure 3). Visit 2 is scheduled as soon as possible from T0 + 28 days at the Paris Brain Institute.

As shown in Figure 3, we collect two types of data: (1) passive behavioural data from sensors, nearly continuously during the four weeks of follow-up; (2) active data from online questionnaires, once a week on a day chosen by the partner who fills the questionnaires (active behavioural data and in patient-caregiver dyads, active data on dyad’s psychological status on a daily scale) and at T0 + 28 days (in patient-caregiver dyads, dyad’s psychological status on a monthly scale).

To retain and support couples included in the study during the four weeks of follow-up, we will schedule two appointments on the phone with an investigator. These appointments will not only allow the investigator to check on the successful completion of the follow-up and to answer the couple’s questions (about technical issues for instance), but they will also provide social support for caregivers who may sometimes feel isolated. Besides, couples included in the study will have the possibility to contact an investigator on business days if needed (see the Instruction and information brochure in Supplemetary Materials, File S2). To further ensure a good quality of data collection, we will reward proper compliance with the protocol through financial compensation (€100 per couple).

